#### Phase 3. Pilot RCT: Intervention Assessment

To evaluate the impact of the resources produced, a pilot RCT will be conducted in the second and third year of the study (Figure 2). The pilot RCT will follow an experimental parallel group design with two arms aiming to assess the impact, feasibility, and acceptability of the resources of Moving Pictures India. The aims of the pilot RCT will be: (1) to test the feasibility of a full RCT with feasibility prespecified as >70% of participants expressing interest, consenting to participate, and >80% participation in follow up; (2) to test acceptability, prespecified as >70% of participants rating the intervention “very acceptable.”

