##### Outcome Measures

The primary outcome measures for the pilot RCT will be feasibility and acceptability, while the secondary outcome measures for the pilot RCT will be (1) caregiver burden, as measured by the Zarit Burden Interview [26]; (2) caregiver mood, as measured by the Center for Epidemiological Studies Depression 10-item scale [27]; and (3) caregiver quality of life, as measured by the World Health Organization Quality of Life Scale [28].

Validated, translated versions of the Zarit Burden Interview and World Health Organization Quality of Life Scale measures are already available in English, Hindi, and several other Indian languages. All the secondary outcome measures will be self-rated and measured at baseline, 3 months, and 6 months via regular mail, telephone, or online. Sociodemographic data (eg, age, gender, socioeconomic status, relation to the person with dementia, years as a caregiver) will also be collected. The schedule of enrolment, interventions, and assessments for the pilot RCT is presented in Figure 3.

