##### Statistical Analysis

To estimate parameters of feasibility and acceptability with sufficient precision, which will help inform the future implementation trial, 40 participants from the intervention arm and 20 from the control arm are expected. The expected values for the proportion of family caregivers rating the intervention as “very acceptable” are 70% (95% CI 59%-87%) or 70% (95% CI 62%-85%) for participants for whom outcomes are completed at the 6-month follow-up. Achieving these expected values will be a priori criteria for progression to an implementation trial without modification of the intervention.

Repeat measures ANOVA will examine changes over time. The proportions of eligible family caregivers approached who agreed to take part in the study will be reported with a 95% CI, and any reasons for refusal will be summarized. Characteristics of people with dementia and their family caregivers that are included in the study will be summarized using means (with SD), medians (with interquartile ranges), counts, and proportions, as appropriate. Scores measured pre- and postintervention will be summarized at each time point (eg, using means and SD) and as differences between the randomization groups with 95% CI. Completeness of these scores will also be described. We will estimate parameters to help inform development of the implementation trial, particularly, the proportion of family caregivers using the intervention and for whom outcomes were completed at the 6-month follow-up.

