### Limitations

Although there are no foreseeable risks associated with participation in this study, there are some factors that may hinder recruitment and participant retention. Digital media is not a common support intervention for caregivers of persons with dementia in India, and acceptance of the program, especially by older caregivers such as spouses, could hamper recruitment. Lack of time to take part in the study due to care responsibilities could also be a factor in retention and recruitment. Nonadherence in eHealth interventions has been reported to be high in earlier studies [37,38]. Another limitation could be that only motivated and active caregivers who are internet or media savvy will take part in the study, which could possibly limit the generalizability of the results and acceptance of the program for the anticipated larger trial. Notwithstanding the limitations, the protocol includes potentially useful approaches for implementation, the most significant of which is the involvement of stakeholders and the utilization of a multifaceted approach involving a mixture of interactive workshops, feedback, reminders, and local consensus processes in the design of the research to ensure relevance [39,40].

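### Repeated-measures ANOVA is a weak choice for the three-visit caregiver scores: it deletes anyone who misses a visit and is aimed at time; a baseline-adjusted mixed model would use the same data better

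*Protocol article*

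**What the plan says.** The protocol article (Methods, Phase 3) describes a pilot with 2:1 allocation: "40 participants from the intervention arm and 20 from the control arm are expected". The three caregiver scales are secondary outcomes, self-rated and "measured at baseline, 3 months, and 6 months via regular mail, telephone, or online" (Outcome Measures).

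The Statistical Analysis section makes three statements about these scores:

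- The only model named is "Repeat measures ANOVA will examine changes over time". The sentence mentions no arm term, covariate or rule for a missed visit.
- Scores are also to be summarised at each time point and "as differences between the randomization groups with 95% CI". Whether these differences are adjusted is not stated.
- On missing scores: "Completeness of these scores will also be described".

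Elsewhere the article foresees some loss. One feasibility criterion is ">80% participation in follow up". The Limitations section names care responsibilities as a threat to retention and adds: "Nonadherence in eHealth interventions has been reported to be high in earlier studies".

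**The concern.** Classical repeated-measures ANOVA needs a complete row for each person. A caregiver who returns the baseline and 6-month questionnaires but misses month 3 leaves the analysis altogether. In a trial of 60, with 20 controls, that is costly.

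The named target is also not the one a randomised comparison exists to estimate. Change over time in caregivers of people with a progressive illness mixes any effect of the films with the course of the illness and regression to the mean. The arm-by-time contrast separates them.

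Finally, a baseline score is collected on everyone, and adjusting for it is the cheapest way to gain precision in a small trial. The article states no such adjustment.

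At stake is the quality of the between-arm estimates for burden, mood and quality of life, outcomes that the article's Results section carries forward to the implementation trial.

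**Working it through.** **Inputs from the article.** 40 and 20 participants; three visits; follow-up just above 80% counts as feasible. The article gives no SD, between-visit correlation, per-visit loss or precision target for these scores, so there is no figure of its own to reproduce. Its only numerical sample-size justification concerns the acceptability proportion and does not enter here.

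**Assumptions.** Scores scaled to SD = 1; correlation ρ between any two visits of 0.3 to 0.7; 20% missing at each follow-up visit; for the simulation, a true effect of −0.4 SD.

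**Step 1: participants kept by classical repeated-measures ANOVA.**

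- The same 20% miss both follow-ups: 60 × 0.80 = 48.
- Misses independent between visits: 60 × 0.80 × 0.80 = 38.4, about 38.

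The loss is therefore 20% to 36% of those randomised.

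**Step 2: standard error (SE) of the 6-month arm contrast, complete data.**

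- Unadjusted difference: √(1/40 + 1/20) = 0.274
- Change from baseline (the 6-month arm-by-time contrast within the ANOVA): 0.274 × √(2(1 − ρ))
- Baseline-adjusted: 0.274 × √(1 − ρ²)

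| ρ | Unadjusted | Change | Adjusted | Gain vs unadjusted | Gain vs change |
|---|---|---|---|---|---|
| 0.3 | 0.274 | 0.324 | 0.261 | 5% | 19% |
| 0.5 | 0.274 | 0.274 | 0.237 | 13% | 13% |
| 0.7 | 0.274 | 0.212 | 0.196 | 29% | 8% |

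At ρ = 0.6 the 95% half-widths are 1.96 × 0.274 = 0.537 SD unadjusted, 0.537 × √0.8 = 0.480 for change and 0.537 × 0.8 = 0.429 adjusted. The gain is 20% against the unadjusted difference but 11% against the change contrast.

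**Step 3: with missing data.** A simulation (1,500 trials per setting) compared the unadjusted difference in those seen at 6 months, the complete-case change contrast, and a likelihood mixed model with constrained baseline and unstructured covariance.

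20% missing completely at random (MCAR), independently at each follow-up visit:

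| ρ | SE unadjusted | SE complete-case change | SE mixed model |
|---|---|---|---|
| 0.3 | 0.296 | 0.424 | 0.290 |
| 0.5 | 0.314 | 0.342 | 0.274 |
| 0.7 | 0.312 | 0.275 | 0.223 |

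No method was materially biased.

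6-month dropout depending on the baseline score in the intervention arm, and random in the control arm:

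| ρ | Bias unadjusted | Bias complete-case change | Bias mixed model |
|---|---|---|---|
| 0.3 | −0.07 | +0.16 | 0.00 |
| 0.5 | −0.12 | +0.12 | 0.00 |
| 0.7 | −0.16 | +0.08 | +0.01 |

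When intervention-arm dropout depended instead on the 3-month score, the unadjusted difference was biased by −0.05 to −0.13 SD. The change contrast and the mixed model were both close to zero.

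**The case against.** The strongest reply is that the criticism rests on one short sentence in a condensed article, and that covariates and missing-data rules normally belong in an analysis plan that is not shown. That stands for detail. It does not dispose of the point, because the article names a model, and an analysis plan that follows the article would inherit it.

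Four stronger readings are tempting, and the article does not support them:

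- **That the plan never estimates the arm contrast.** It does, as group differences with 95% CIs. Only the ANOVA sentence is aimed at time, and the per-visit differences need not drop someone who missed a different visit.
- **That baseline is ignored.** Baseline is one of the three ANOVA time points, and the text is silent on adjustment rather than excluding it.
- **That a mixed model is less biased in general.** Under MCAR there was no bias to remove. If dropout depends on unobserved current burden (missing not at random, MNAR), the mixed model is not protected either.
- **That precision improves by a fifth over the ANOVA.** That figure compares adjustment with an unadjusted difference at ρ = 0.6; against the change contrast the gain is 11%.

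Two further points stand. If the same people miss both follow-ups, a model with baseline as a covariate recovers nobody, and its gain comes from adjustment alone. And nonadherence to an intervention, which the Limitations section cites, is not the same as a missed questionnaire.

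**Conclusion.** The point holds in limited form. Repeated-measures ANOVA of change over time is the only model named for three-visit scores in a trial that itself foresees loss. Its classical form would keep about 38 to 48 of 60 participants if 20% are missing at each follow-up visit, and its stated target is not the arm-by-time contrast. A baseline-adjusted mixed model had the smallest SE in every setting examined. With complete data the reduction is 5–29% against an unadjusted difference and 8–19% against a change contrast, for ρ from 0.3 to 0.7.

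All these sizes rest on assumed correlations and dropout. The gain in bias is confined to dropout that depends on observed scores. The effect is limited to secondary outcomes and to estimates that may inform the later trial. Feasibility, acceptability and the progression criteria are unchanged.

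**What to change.** Replace the ANOVA sentence with wording such as:

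> Burden, mood and quality-of-life scores will be analysed with a likelihood-based linear mixed model using all available scores, with terms for arm, visit, arm-by-visit and baseline. The baseline-adjusted difference between arms at 6 months will be reported with its 95% CI as an estimate, not as a test of effectiveness.

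Baseline can enter as a covariate, in which case participants with no follow-up score contribute nothing. Alternatively it can enter as an outcome whose mean is constrained to be equal between arms, which keeps participants who have only a baseline score. State which is used. Say also whether the between-arm differences already promised are these adjusted estimates or unadjusted descriptive ones. Covariance structure and degrees of freedom can be left to the analysis plan.

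The cost is a change of wording and slightly more analysis work, with no new data, participants or visits.

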##### Postpilot Revision

If required, specific changes based on the research team’s postpilot experience and participant feedback will be incorporated into the intervention before dissemination of the resources.

#### Phase 4. Dissemination and Analytics: Intervention Dissemination

Following postpilot minor revisions (if any), all the resources developed in the study will be disseminated via the mobile-optimized Moving Pictures website. Key stakeholders (eg, the Indian Ministries of Health and Social Justice, state and local government health and welfare offices, Alzheimer’s and Related Disorders Society of India, Alzheimer’s International; Alzheimer’s Association in the United States, community groups, health services, and media) and consumers (caregivers, people with dementia, and the general public) will receive a media release with links to the website. Social media campaigns will also be run at regular intervals on Facebook, YouTube, WhatsApp, and Twitter. To evaluate the reach and uptake of these digital resources, analytics data will examine website traffic and viewing trends over 6 months. The feedback in the comment sections will be reviewed and visits to the website will be counted. A flowchart of this phase is illustrated in Figure 4.

**Figure 4 figure4:**
[figure not shown]
Study protocol flowchart of phase 4: dissemination and analytics.

### Ethics Approval

The procedures outlined in this study are in accordance with the Declaration of Helsinki, and this study has been approved by the NIMHANS Ethics Committee (26th IEC (BEH.SC.DIV.)/2020-21 dated November 11, 2020); the Health Ministry's Screening Committee, India (proposal ID 2020-10137); the Curtin University Human Research Ethics Committee (approval number HRE2020-0735); and the NARI Research Governance Office (site-specific approval dated March 17, 2021).

### Data Storage and Transfer

As the data are being collected in India, data will be stored securely onsite; specifically, hard copy data will be stored in a locked filing cabinet in the office of the investigators. Signed documents will be converted to electronic files, which will then be password protected and stored on the secured NIMHANS network. When in the field, data will be stored on the research staff member’s laptop, which is password protected and backed up to an external hard drive that will also be password protected if required. All data (hard and soft copies) will be stored securely stored and destroyed 7 years after publication. Electronic copies of all data will be securely shared with the Australian research team. During data analysis and write-up, the data will be stored on a secured server in the password-protected folder only accessible by the Moving Pictures research team. Upon completion, all data will be securely transferred and stored under secure conditions at Curtin University and NARI, Australia, for 7 years after the research is published and then securely destroyed.

### Project Dissemination

Data will be published in deidentified form in academic and other publications (book chapters, conference presentations, media releases, social media posts, etc) under pseudonyms or participant IDs. For example, the participant might be described in the following manner: Asha Chand (pseudonym), female, age, caregiver for mother. Data used in films and resources may be identifiable, as we will be using the video data from the interviews in the resources. Caregivers will be assigned pseudonyms, and health providers will be using their own names and affiliations as specified in the PICFs. The films will be accessible via the Moving Pictures website to anyone in the community, and efforts will be made to disseminate the resources as broadly as possible. There are no plans to make the dataset publicly available after deidentification.

## Results

This study was funded by the Alzheimer’s Association. It brings together complementary expertise across multiple disciplines such as anthropology, psychology, psychiatry, geriatrics, film and media studies, disability studies, and social work.

Postdissemination analytics and qualitative feedback will be used to develop an implementation trial; explore how different strategies for dissemination and integrating the resources in local service provisions impact relevant caregiver variables like caregiver burden, mood, and quality of life; and evaluate the effects of the approaches to improve the uptake and utilization of the intervention. From July to December 2023, we will enroll 60 dementia caregivers (40 caregivers in the intervention group and 20 in the control) for the pilot RCT and follow them up for 6 months. This study is expected to conclude in June 2024.

## Discussion

### Overview

Although dementia has been recognized as a global public health priority, a huge gap between dementia care needs and resources still exists, especially in low- and middle-income countries. There is a clear need for the development of dementia literacy and care resources that emphasize identifying dementia through awareness, offer interventions to manage the symptoms of dementia, and promote well-being of both the caregiver and the person with dementia. In this paper, we have outlined the design of an intervention study that involves the development of a digital media resource to improve dementia care in India and determine the feasibility and acceptability of the developed resource using an RCT design. This study will be one of the first to deliver coproduced, evidence-based media resources to support caregivers of people with dementia in the Indian context.

### Comparison With Prior Work

The flexible, nonlinear approach of the UK Medical Research Council framework that guides the methodology of this study has previously been used in the design processes for the development of new technology-based interventions across disciplines [29-31]. This protocol emphasizes the importance of all the stages involved in developing and evaluating complex interventions, such as Moving Pictures India, and provides equal focus on development and piloting work as it does to the evaluation and proper consideration of the practical issues of implementation.

Through the process of coproducing films, we will gain an understanding of how dementia is perceived cross-culturally. This is an important aspect for dementia literacy and care, as dementia in India is typically viewed as a natural part of aging with cultural explanations used to describe dementia such as “chinnan” (childishness) [32]. The outcomes defined for the study, as well as the instruments to measure the outcomes, have been used in earlier studies with caregivers of people with dementia [29,33-36].

### Limitations

Although there are no foreseeable risks associated with participation in this study, there are some factors that may hinder recruitment and participant retention. Digital media is not a common support intervention for caregivers of persons with dementia in India, and acceptance of the program, especially by older caregivers such as spouses, could hamper recruitment. Lack of time to take part in the study due to care responsibilities could also be a factor in retention and recruitment. Nonadherence in eHealth interventions has been reported to be high in earlier studies [37,38]. Another limitation could be that only motivated and active caregivers who are internet or media savvy will take part in the study, which could possibly limit the generalizability of the results and acceptance of the program for the anticipated larger trial. Notwithstanding the limitations, the protocol includes potentially useful approaches for implementation, the most significant of which is the involvement of stakeholders and the utilization of a multifaceted approach involving a mixture of interactive workshops, feedback, reminders, and local consensus processes in the design of the research to ensure relevance [39,40].

### Conclusions

This research protocol directly addresses a looming public health crisis in India by promoting dementia awareness and developing resources to support caregivers in delivering high-quality care at home. It offers solutions that are culturally specific, scalable, and based on knowledge of local resources and burden of disease [41]. Thus, it has the potential to improve the lives of millions of people in India. The design selected leverages India’s significant online presence, and resources will be available to those who have difficulty accessing face-to-face information and support on account of being too busy, having difficulty traveling, and/or living in rural areas. Importantly, the lessons learned from this study are highly transferable. India also has a diaspora of 30 million people, the largest in the world [42]. Concerns regarding suboptimal dementia care in Indian communities have been expressed by caregivers and key service providers in the Moving Pictures Australia study [16]. Similar concerns have also been echoed from studies in the United Kingdom and Canada [43,44]. With the integrated insights from Moving Pictures Australia and Moving Pictures India, this protocol will yield an intervention that will be transferrable to multiple diaspora communities in low-, middle-, and high-income countries and will explore how different strategies for dissemination and integrating resources in local service provisions could impact caregiver burden, mood, and quality of life.

## Appendix

Multimedia Appendix 1 Blinded peer-review assessment scores and comments from the Alzheimer's Association Research Grant Review Committee - Alzheimer's Association Research Grant (AARG).

## Abbreviations

NARI: National Ageing Research Institute
NIMHANS: National Institute of Mental Health and Neuro Sciences
PICF: participant information and consent form
RCT: randomized controlled trial
